### Intervention and treatment integrity, feasibility and satisfaction

The same manualized ACT intervention will be delivered to both intervention groups, consisting of 13 individual weekly sessions delivered online through videoconference; this is mandatory for investigating if the same intervention similarly impacts outcomes in participants presenting with diverse diagnostics. The intervention will be developed based on the PF model of ACT [37] and the choice-point model [82], and it will result from the adaptation of the *ACT@TeenSAD* intervention for adolescents with SAD (a 10-session manualized ACT intervention delivered online; Vagos et al., 2021), as well as the integration/modification of sessions’ exercises based on extensive research on ACT, ACT for ADs, and ACT for adolescents, and on the research team’s clinical expertise with adolescents and in delivering ACT based interventions. The ACT intervention for adolescents with ADs will include sessions addressing the functioning of the human mind (e.g., the survival machine, the problem-finding and problem-solving machine), creative hopelessness, the six core processes of PI/PF (e.g., acceptance of difficult thoughts, emotions, and sensations, values clarification), and revision of gains and relapse prevention (cf. Table 1). Each session will have an approximate duration of 1 hour and will be composed of experiential exercises, metaphors, images, and mindfulness practices targeting the specific topic of the session. Participants will be invited to complete between-session tasks as often as they can, in order to practice the strategies addressed in each session (e.g., present moment awareness practices) in real-life contexts. Several aspects will be taken into consideration by the research team members when developing and implementing the intervention to ensure treatment integrity. For example, the research team will seek training in ACT-based approaches, ongoing supervision by experienced psychologists, inclusion of clear and informative descriptions of exercises, as well as therapist lines (e.g., examples of questions to guide adolescents) in the intervention manual, and therapist’s report on treatment adherence after each session.

**Table 1 Tab1:** Intervention Outline

Session	Contents
1	The human mind and the ACT model: psychoeducation on the nature and functioning of the human mind from an evolutionary perspective, functional assessment, and development of an individualized model to recognize the PI processes maintaining adolescents’ difficulties using the choice-point model
2	Creative hopelessness: reflecting on the costs and workability associate with the control agenda and introducing the possibility of alternative strategies (i.e., brief introduction to the PF processes)
3	Values: exploring the importance of values clarity in one’s life, clarifying the concepts of values (vs goals), identifying adolescents’ personal values and related committed actions (in low anxiety provoking situations)
4	Present moment awareness: reflecting on the role of intentionally contacting the present moment and practicing contact with the present moment in the absence and presence of difficult internal experiences
5	Cognitive defusion: exploring the true nature of thoughts, the impact of hooking and unhooking from them and experimenting different unhooking techniques
6	Acceptance: reflecting on the importance of willingness to contact with difficult emotions and sensations and developing acceptance skills by engaging in multiple exercises
7	Observing-self: introducing the concept of self as a stable and distant observer of the ongoing flow of internal experiences and cultivating this perspective through guided exercises
8–12	ACT informed exposure (committed action): defining stimuli to be exposed to in-session that align with adolescents’ values, identifying obstacles (i.e., PI processes) and helpers (i.e., PF processes related strategies), and conducting exposure exercises
13	Revision of gains and relapse prevention: reflecting on the journey up to this moment, revising the adolescent values and identifying future committed actions, potential obstacles and learned strategies to deal with future difficulties

Sessions will be delivered individually and weekly, with an approximate duration of 1 h each. Metaphors, and/or experiential exercises will be used to address the contents of each session. Between-sessions exercises and practices will also be included

The feasibility of the program will be further assessed through the examination of dropout and adherence rates. Concerning program acceptability and participants’ satisfaction, a questionnaire will be used to assess adolescents’ satisfaction after completing the 13 sessions. The questionnaire comprises 5 items (e.g., “themes addressed in sessions”, “sessions length”) answered on a 5-point Likert scale, assessing the degree to which the participant believes each aspect was adequate, useful and/or relevant (responses ranged from 1 = nothing, to 5 = a lot). This questionnaire also includes three open-ended questions: “what three things did you like the most about the program?” and “what three things did you like the least about the program?” and “if you could change three things about the program, what would it be?”.

### Measures

Participants will be asked to complete a sociodemographic information sheet to assess age and date of birth, biological sex, parent’s professions, area of residence (rural/urban), years of education and grade retentions, existing mental health difficulties (yes/no; if yes, provide a brief description) and current/past psychological support/interventions (yes/no; if yes, describe the motive).

#### Screening and inclusion/exclusion criteria

**Screen for Child Anxiety Related Disorders (SCARED; **[79, 83] The SCARED is a 41-item self-report questionnaire that assesses symptoms of anxiety disorders. Items (e.g., “I worry about other people liking me”) are answered on a 3-point Likert scale (ranging from 0 = ’Almost Never’ to 2 = ’Often’). The SCARED comprises 5 subscales that allow to screen for the following anxiety disorders: generalized anxiety, separation anxiety, somatic/panic, social phobia, and school phobia. The SCARED has shown good internal consistencies, with Cronbach’s alpha values over 0.78 for the total score and subscales [83]. In its Portuguese version [79], the SCARED Total and the SCARED Reduced Total score (i.e., items and scales with poor Cronbach alphas were excluded,consists of 28 items revealed good internal consistencies, with Cronbach’s alpha values of 0.87 and 0.85, respectively. The Generalized Anxiety and the Social Phobia subscales, which will be used in the present study along with the Reduced Total Score, also presented acceptable internal consistencies (i.e., Cronbach’s alpha values of 0.71 and 0.74, respectively; [79]. Evidence for SCARED Portuguese version convergent validity has been found in relation to measures of anxiety and depression symptomatology. Specifically, the SCARED Reduced Total Score and the Generalized Anxiety and Social Phobia subscales presented expected higher correlations with anxiety, compared to the associations with depression [79].

**Mini International Neuropsychiatric Interview for Children and Adolescents (Mini-KID; **[78, 84]). The Mini-KID is a structured diagnostic interview for the assessment of DSM-5 Axis I diagnoses in children and adolescents. Questions answered in a YES/NO format are presented for the evaluation of specific diagnostic criteria for each clinical diagnosis. In the original version of the Mini-KID, interrater reliability was excellent across diagnoses, except for dysthymia [78]. The Portuguese version of the Mini-KID resulted from a careful translation and backtranslation process and has been previously used as a method for the assessment of clinical diagnoses [85].

#### Primary outcomes

**Generalized Anxiety Disorder – 7 (GAD-7; **[86, 87]). The GAD-7 is a 7 item self-report scale initially designed to identify probable cases of Generalized Anxiety Disorder (GAD). Items (e.g., “Feeling nervous, anxious or on edge”) are answered in a 4-point Likert scale (ranging from 0 = ’not at all’ to 3 = ‘nearly every day’) reporting to the two previous weeks, with higher scores representing higher levels of GAD symptoms. In its original version [86], the GAD-7 presented a Cronbach’s alpha of 0.92 and evidence for its construct validity was found in relation to measures of anxiety, depression, and health-related quality of life. In its Portuguese version for children and adolescents [87], the GAD-7 achieved a Cronbach’s alpha value of 0.93, and higher scores on the GAD-7 were associated with lower quality of life and lower satisfaction with school.

**Social Anxiety and Avoidance Scale for Adolescents (SAASA; **[88]**)**. The SAASA consists of 34 items assessing the degree of anxiety and frequency of avoidance in social situations representative of the most frequent social fears during adolescence. Each item (e.g., “Going to a party given by a colleague”) is answered twice, for two subscales – anxiety and avoidance -, on a five-point Likert scale (ranging from 1 = ‘none’ to 5 = ‘very much’, for anxiety; and from 1 = ‘never’ to 5 = ‘almost always’, for avoidance). Each subscale is comprised of six factors: interaction with the opposite sex, assertive interaction, observation by others, interaction in new social situations, performance in social situations, and eating and drinking in public. In its validation study, the SAASA total score and subscales achieved Cronbach’s alpha values over 0.61 [88]. The SAASA has also demonstrated good test–retest reliability, convergent and divergent validities in relation to measures of anxiety, social anxiety and depression, capacity to discriminate adolescents with SAD from adolescents with other anxiety disorders and adolescents without psychopathology [88], and sensitivity to treatment results [89].

#### Secondary outcomes

**Multidimensional Psychological Flexibility Inventory – short form (MPFI—24; **[90, 91**]).** The MPFI-24 is a 24-item self-report scale for the assessment of PI and PF. The scale comprises 12 subscales, representing the processes underlying PF (i.e., Acceptance, Present Moment Awareness, Self as Context, Defusion, Values, Committed Action) and PI (i.e., Experiential Avoidance, Lack of Contact with the Present Moment, Self as Content, Fusion, Lack of Contact with Values, Inaction). Items (e.g., “I opened myself to all of my feelings, the good and the bad”) are answered on a 6-point Likert scale (ranging from 1 = ‘never true’ to 6 = ‘always true’) regarding how true the item was for the respondent in the previous 2 weeks. Each subscale items can be averaged to represent each of the 12 specific dimensions of PF and PI. Likewise, the averages of the 6 flexibility and 6 inflexibility subscales can be averaged to create a composite score representing global flexibility and inflexibility, respectively. Evidence was found favoring the MPFI-24 convergent validity in relation to other measures of PF and PI processes. Also, the subscales and composites have achieved adequate to good internal consistency values [90]. The MPFI-24 Portuguese version for adolescents presented acceptable to good internal consistency values for the subscales and good to excellent internal consistency values for the composites [91].

**Mental Health Continuum – Short Form – for youth (MHC-SF; **[92]**)**. The MHC-SF is a 14 items self-report measure that assesses adolescents’ flourishing based on levels of subjective well-being across 3 domains: emotional, social and psychological well-being. Following the instructions (“Please answer the following questions about how you have been feeling during the past month”), items (e.g., “How often do you felt happy?”) are answered on a 6-points Likert scale (ranging from 0 = ’Never’ to 5 = ’Every day’). In its original version, the MHC-SF domains presented Cronbach’s alphas between 0.78 and 0.84 [93]. In its Portuguese version [92], factors achieved Cronbach’s alpha values ranging from 0.80 to 0.85, and the total score representing flourishing presented a Cronbach’s alpha value of 0.90. Moreover, factors presented expected positive associations with measures of quality of life and life satisfaction, and negative associations with measures of anxiety, depression, and internalizing and externalizing problems [92].

### Data analysis

IBM SPSS Statistics 25 will be used to conduct descriptive analysis. In study I, network analysis will be performed and visualized using R (Version 4.1.3). Network nodes will represent the scores for each PI/PF subscales and total scores for anxiety and flourishing measures. Edges will represent the weight of the correlations between the individual nodes. Centrality metrics (e.g., degree of centrality) will also be computed to investigate how important and influential each node is in the network. In study II, Mplus will be used to investigate the adjustment of a path analysis linking PI/PF processes to anxiety and flourishing, based on overall, comparative and residual based fit-indices. The moderator effect of groups (clinical SAD, clinical GAD and healthy adolescents) in those pathways will be estimated, testing for equality of pathways and means. In Study III, the IBM SPSS Statistics 25 will be used to explore treatment effects using Mixed ANOVAs and considering assessment moments as the within-subject and groups (SAD and GAD receiving intervention and Control Groups) as the between-subject effect; interaction effects will also be considered. Additionally, Mplus will be used to examine mechanisms of change after the intervention by performing two-wave latent change score models. These models allow to explore not only if significant changes emerged across assessment moments, but also to investigate the impact of changes in PI/PF constructs on changes in anxiety or flourishing. All Study III analyses will be carried out according to an intention-to-treat principle as suggested by the CONSORT guidelines [77]. Therefore, all participants randomized will be included in the statistical analyses and analyzed according to the group they were assigned regardless of having received/completed or not the intended intervention. Efforts will be made to obtain outcome data for all participants, even if they do not complete the intervention. If data is missing (e.g., participant refused to provide data, participant was unreachable, etc.) the last observation carried forward method will be employed.

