As a second aim of the current work, we intend to contribute to filling the gap on the efficacy of ACT as a transdiagnostic approach to adolescents' SAD and GAD and amplify the transdiagnostic application of ACT to adolescents presenting these disorders (Study III). To do so, we will adapt, implement, and investigate the efficacy of an ACT Intervention to adolescents presenting SAD or GAD by exploring:Changes in primary (i.e., anxiety symptoms) and secondary (i.e., flourishing and PI/PF processes) outcomes following intervention. In view of the scarce but promising research on ACT efficacy in adolescents’ SAD [60, 74, 75], and GAD [60], improvements are expected at post-intervention for the two intervention groups (i.e., SAD and GAD), in comparison with a control group.The stability of change over time (i.e., 3 and 6 months after intervention completion). We expect improvements in the two intervention groups to be maintained.The equivalence of the efficacy of the same intervention delivered to the two intervention groups (i.e., SAD and GAD). Even though this aim has not yet been addressed, considering ACT conceptual and therapeutic transdiagnostic premises, similar effects on outcome measures are expected for both clinical groups.Mechanisms of change following the intervention in both intervention groups. Based on research conducted with adults on PI/PF processes as mechanisms of change following ACT [43], we expect similar effects in both intervention groups, with changes in PI/PF predicting changes in primary (i.e., anxiety symptoms) and secondary (i.e., flourishing) outcome variables. Specifically, we expect increases in PF processes and decreases in PI processes to promote lesser anxiety and greater flourishing. Given the lack of research on the role of each PI/PF process in producing changes in anxiety for adolescents’ GAD and SAD and the ACT assumptions that all processes are intertwined in their contribution to human suffering / flourishing [38], there were no grounds to define specific hypothesis regarding the differential role of each PI/PF process in contributing to decreases in anxiety and increases in flourishing between the two samples of adolescents, and so no specific and process-based hypotheses are put forward.

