### Study design and randomization of participants

The two aims of this research will be accomplished through diverse study designs. To accomplish the first aim, cross-sectional data will be collected from adolescents within a community sample, two clinical groups (with SAD or GAD), and a mentally healthy sample. For the second aim, a Randomized Controlled Trial (RCT) with a parallel design, 3 groups (i.e., Control Group, SAD Intervention Group, and GAD Intervention Group) and 4 assessment moments will be conducted following the CONSORT (Consolidated Standards of Reporting Trials) guidelines [77]. Adolescents from each clinical group from Study II will be randomly allocated (computer-generated random allocation,2:1 allocation ratio) to one of the intervention groups or to the control group. The two clinical intervention groups will receive the same intervention and will be assessed at pre- and post-intervention, and at 3- and 6- month follow-up using a set of self-report measures (see measures section). Adolescents from the control group will be assessed with the same set of self-report measures at 2 different time points (12 weeks interval), mimicking the pre- and post-intervention assessment moments. Given the high stability of both SAD and GAD, we consider ethical obligations to be imperative in not depriving these adolescents of intervention during follow-up assessments. As such, they will be assessed with a clinical structured interview (Mini-Kid; [78]) after the second time point and referred to the school psychology services if the difficulties persist. A flowchart of the study design is presented in Fig. 1.

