### Sample size

Participants recruited in Study II will be randomly assigned to one of the three groups of Study III (cf. Figure. 1). G*Power was used to calculate sample size considering Study III requirements for repeated measures analysis with two groups (considering that the RCT groups will be compared two at a time) and 4 assessment moments. Power analysis for medium effects (f = 0.25) – chosen based on previous ACT studies with adolescents (e.g., [27–30, 60, 80]) –, with a significance level of 0.05 and power of 0.95 requires a sample size of 25 per group. To account for the expected 17% dropout rate reported in a previous meta-analysis of ACT-based interventions [81], the research team intends to collect 4 additional participants per group. Accordingly, Study II will rely on two clinical groups (i.e., SAD and GAD,n ≥ 87) of at least 44 adolescents each, and a mentally healthy group of 29 adolescents (i.e., total n for Study II ≥ 116). For Study III, the clinical participants (i.e., n ≥ 87) will be then assigned to two intervention groups of 29 adolescents each, one for SAD and one for GAD participants, or to a control group of 29 adolescents, evenly distributed between adolescents presenting with SAD or GAD diagnoses.

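### The Mixed ANOVA efficacy test against control makes no use of the baseline as a covariate and so gives away precision that a baseline-adjusted model would keep

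*Protocol article*

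**What the plan says.** - **Efficacy method** (Data analysis): "the IBM SPSS Statistics 25 will be used to explore treatment effects using Mixed ANOVAs". Assessment moment is the within-subject factor and group enters "as the between-subject effect; interaction effects will also be considered". No baseline covariate is named.
- **Assessments** (Study design and randomization of participants): the intervention groups "will be assessed at pre- and post-intervention, and at 3- and 6- month follow-up". Controls are assessed "at 2 different time points (12 weeks interval), mimicking the pre- and post-intervention assessment moments". Allocation is random and 2:1 within each diagnosis.
- **Efficacy hypothesis** (AIMS): "improvements are expected at post-intervention for the two intervention groups (i.e., SAD and GAD), in comparison with a control group".
- **Sample size** (Sample size): the basis is "repeated measures analysis with two groups (considering that the RCT groups will be compared two at a time) and 4 assessment moments", with f = 0.25, alpha 0.05 and power 0.95, giving 25 per group and 29 after an allowance for dropout. The control group of 29 is split evenly between the two diagnoses.

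**The concern.** Efficacy is judged at post-intervention against a control group that has two assessments. In that layout the Mixed ANOVA interaction is a change-score analysis. A change score subtracts the whole baseline, whatever the correlation between pre and post. A baseline-adjusted model subtracts only the part that predicts the post score, so with similar SDs its residual variance is smaller for any rho below 1.

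The article does not leave the model open: it names one, and the criticism is of that choice. The arms are small, the limitations in the Discussion expect dropout to be a significant challenge, and the baseline of every outcome is collected anyway. What is at stake is power, the width of the confidence intervals, and protection against chance baseline imbalance.

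**Working it through.** **Inputs.** From the article: 2 groups compared at a time, 4 moments in the power calculation, f = 0.25, alpha 0.05, 25 per group, 29 randomised per group, 2 moments in controls. From 2:1 allocation of 44 adolescents per diagnosis: about 29 intervention and 15 control (29 + 15 = 44). Assumed: rho from 0.3 to 0.8, and equal pre and post SDs.

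**1. The stated sample size.** For the within-between interaction of a repeated-measures ANOVA, lambda = f² × N × m/(1 − rho), with df (k − 1)(m − 1) and (N − k)(m − 1). With k = 2, m = 4, N = 50 and rho = 0.3, lambda = 0.0625 × 50 × 4/0.7 = 17.86 and power is 0.952. So 25 per group reproduces, but only at rho = 0.3, which the article does not state; rho = 0.5 would give 18 per group.

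**2. What f = 0.25 means over two moments.** With m = 2, lambda = 0.0625 × 50 × 2/0.7 = 8.93. A t test on change has squared noncentrality D²/[2(1 − rho)(1/25 + 1/25)] = D²/(1.4 × 0.08) = 8.93 D². The two agree at D = 1.0, so f = 0.25 is a 1.0 SD difference in change. The power is also identical, 0.833, as expected when the interaction is the change-score t test.

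**3. Variance comparison**, in units of SD²:
- change score: 2(1 − rho)
- post adjusted for baseline: 1 − rho²
- ratio: (1 − rho)(1 + rho)/[2(1 − rho)] = (1 + rho)/2

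| rho | change | adjusted | reduction |
|---|---|---|---|
| 0.3 | 1.40 | 0.91 | 35% |
| 0.5 | 1.00 | 0.75 | 25% |
| 0.7 | 0.60 | 0.51 | 15% |
| 0.8 | 0.40 | 0.36 | 10% |

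**4. Power in layouts that respect diagnosis** (noncentral t, two-sided 0.05, one df for the covariate). Example for 29 versus 15 at rho 0.3 and 1.0 SD: 1/29 + 1/15 = 0.1011. The noncentrality is 1/√(1.40 × 0.1011) = 2.66 for change and 1/√(0.91 × 0.1011) = 3.30 adjusted.

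| Layout | Difference | rho 0.3 | rho 0.5 | rho 0.7 |
|---|---|---|---|---|
| Within diagnosis, 29 v 15 | 1.0 SD | 0.74 → 0.90 | 0.87 → 0.94 | 0.98 → 0.99 |
| Within diagnosis, 29 v 15 | 0.5 SD | 0.26 → 0.36 | 0.34 → 0.43 | 0.51 → 0.58 |
| Both arms v control, 50 v 25 | 1.0 SD | 0.93 → 0.99 | 0.98 → 0.996 | not tabulated |

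The 29 versus 15 figures use randomised numbers before dropout. The 50 versus 25 figures use the article's 25 per group.

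**5. If the group main effect were the test.** It averages a pre-treatment score into the outcome. For a 1.0 SD post difference and 25 per group, the effect on the average is 0.5 SD with variance (1 + rho)/2, and power is 0.57, 0.52 and 0.47 at rho 0.3, 0.5 and 0.7. That reading does worse than the interaction.

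**The case against.** - **The size of the gain rests on an unstated correlation.** This stands. The value 0.3 is only back-solved from the sample size. The article's remarks on the high stability of both disorders and on SAASA test–retest reliability point higher. At rho 0.7 and 1.0 SD both tests are close to saturation, and the gain shows mainly for smaller effects.
- **Equal SDs are assumed.** This stands. Selection on high screening scores may narrow the baseline spread. If the pre SD were 0.85 of the post SD, the reductions at rho 0.3, 0.5 and 0.7 would be 25%, 14% and 4%; at 0.7 of the post SD, 15%, 5% and 0%.
- **A reader might infer that adjustment restores the planned 95% power**, because 25 versus 25 at rho 0.3 gives 0.952 adjusted against 0.833 for change. The design does not support this. Each intervention arm has one diagnosis and the control group has two. With diagnosis in a pairwise model, only same-diagnosis controls inform the arm effect, about 25 versus 12.5. Adjusted power for 1.0 SD is then 0.84, 0.90 and 0.98 at rho 0.3, 0.5 and 0.7. The 25 versus 25 change score has 0.83, 0.93 and 0.99, but it compares unlike diagnosis mixes. Compared like for like, adjustment still wins.
- **The interaction is not expressly named as the efficacy test.** True: interactions are to be considered as well. Step 5 shows that the alternative is weaker.
- **Covariates are commonly left to an analysis plan.** Often so, but here the article names a complete model without one.

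**Conclusion.** The point holds as a loss of efficiency in the randomised post-intervention comparison with control. Given randomisation within diagnosis and similar pre and post SDs, the change-score test carries 2/(1 + rho) times the variance of the adjusted model. The adjusted model has higher power in every like-for-like layout tabulated. The gain is material at low to moderate rho and small at 0.7 or above when the true difference is 1.0 SD.

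Three stronger conclusions are not supported:
- that the Mixed ANOVA is biased or invalid here: under randomisation it is a valid test of change;
- that the argument covers the SAD-versus-GAD comparison, which is not randomised, or the maintenance analysis over follow-up, where controls have no data;
- that adjustment repairs a control group with a different diagnosis mix, or by itself secures 95% power for single-diagnosis contrasts.

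**What to change.** Name a baseline-adjusted model as the primary analysis of the post-intervention comparison with control. There are two equivalent routes:
- post score = arm + baseline score, fitted separately within SAD and within GAD; or
- post score = arm + diagnosis + baseline score, fitted on all randomised participants.

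Report the adjusted mean difference with a 95% confidence interval for each primary outcome, and treat flourishing and the PI/PF scores the same way. Keep the Mixed ANOVA as supportive. State the pre-post correlation assumed, and give power for the contrast actually made (about 29 versus 15, or both arms pooled against control).

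The cost is a change of wording in the analysis section, made before outcome data are seen. It needs no extra participants, visits or measures.

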
This study presents some foreseen limitations that are, nevertheless, necessary for its viability. Firstly, it focuses solely on SAD and GAD, disregarding other ADs that also present significant prevalence rates and impairments during adolescence. Additionally, the control group will not receive intervention within this project. To ensure these adolescents receive appropriate care, they will be assessed after completing the control condition and referred to school psychology services if difficulties persist. They will also be explicitly informed about the possibility of discontinuing their participation in the study to seek treatment, without any consequences. It is also important to note that the control group may not be entirely comparable to either of the intervention groups, which could lead to inherent disparities and the introduction of potential confounding variables. Based on ACT transdiagnostic premises, we believe that these differences will not significantly influence our findings. Nevertheless, the authors have devised a contingency plan to address this potential limitation, if necessary (i.e., gathering two independent control groups: one consisting solely of adolescents with SAD and another comprising only adolescents with GAD). We also acknowledge that by only using self-report measures, data collection may be susceptible to the effects of social desirability, and only a limited comprehension of the psychological constructs assessed is provided. Moreover, we anticipate dropouts to be a significant challenge in this study. To prevent its impact, the research team plans to recruit more participants than the minimum needed for each condition. This approach will allow us to account for potential attrition and ensure that sample size remains adequate throughout the study, maintaining statistical power. Efforts will be made to engage and motivate participants throughout the duration of the study to maximize retention rates (e.g., by sending thank you messages after each assessment moment). Lastly, we acknowledge that by not considering a group with comorbid GAD and SAD, we cannot fully elucidate the applicability of transdiagnostic principles to adolescents. Future research should consider comorbidity and/or cascading effects of mental health difficulties as relevant outcomes to better address the complex issues related to ACT as applied to adolescent mental health.

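### Each single-diagnosis intervention group is compared with a mixed SAD/GAD control group although allocation is within diagnosis, so the efficacy contrasts can be confounded by diagnosis

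*Protocol article*

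**What the plan says.** **Allocation.** The section on study design and randomisation states: "Adolescents from each clinical group from Study II will be randomly allocated", at a 2:1 ratio, to the intervention group or to control. An adolescent with SAD can enter SAD-ACT or control; one with GAD can enter GAD-ACT or control.

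**Groups.** The Sample size section plans "two clinical groups (i.e., SAD and GAD,n ≥ 87) of at least 44 adolescents each". These are split into "two intervention groups of 29 adolescents each, one for SAD and one for GAD participants", and "a control group of 29 adolescents, evenly distributed between adolescents presenting with SAD or GAD diagnoses". The same section says the trial groups are compared in pairs.

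**Analysis.** The Data analysis section specifies mixed ANOVAs with assessment moment as the within-subject factor and "groups (SAD and GAD receiving intervention and Control Groups) as the between-subject effect". Interactions are to be considered. The model has no term for the controls' diagnosis.

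**Hypothesis.** Under Aims, improvement is expected in each of the two intervention groups relative to a control group.

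**Disclosure.** The Discussion concedes that the control group may not be fully comparable with either intervention group and that confounding could follow. It expects little effect, on ACT's transdiagnostic premises, and offers a contingency if needed: "gathering two independent control groups: one consisting solely of adolescents with SAD and another comprising only adolescents with GAD". No trigger or method of allocation is given for it.

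**The concern.** Allocation within diagnosis creates two randomised comparisons: SAD-ACT against SAD controls, and GAD-ACT against GAD controls. The planned analysis makes neither. It sets an all-SAD group, and separately an all-GAD group, against a control group in which about half the members have the other diagnosis.

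Diagnosis is likely to matter for these outcomes. Each clinical group is selected by a high score on its own SCARED subscale and then by diagnostic interview, and adolescents with both disorders are excluded. GAD-7 was built to identify GAD, and the Measures section credits SAASA with separating SAD from other anxiety disorders. Different levels by diagnosis are therefore to be expected, and different untreated change is possible.

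If untreated change does differ, the planned contrast mixes that difference with the effect of ACT. Because the bias has opposite signs in the two contrasts, ACT could appear to work in one disorder and not the other. That would distort the transdiagnostic conclusion.

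**Working it through.** **1. The plan's own figures.** The allocation arithmetic reproduces: 3 x 29 = 87; 87/2 = 43.5, rounded up to 44 per diagnosis; 44 x 2/3 = 29.3 to ACT and 44/3 = 14.7 to control. The control group is therefore about 15 + 14.

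The 25 per group (two groups, four moments, f = 0.25, alpha 0.05, power 0.95) depends on a correlation between repeated measures that is not stated. For the within-between interaction, lambda = f² x N x m/(1 - rho). With N = 50, m = 4 and rho = 0.3, lambda = 0.0625 x 50 x 4/0.7 = 17.9 and power is 0.952, so 25 per group is reproduced. At rho = 0.5, 18 per group would suffice. I therefore show 0.3 and 0.5 below, as assumptions.

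**2. Bias of the change contrast.** Let D be untreated change in SAD minus untreated change in GAD. With no treatment effect:

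- SAD-ACT minus control = D x (share of GAD among controls) = D x 14/29 = 0.48D
- GAD-ACT minus control = -D x (share of SAD among controls) = -D x 15/29 = -0.52D

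Each is about half of D, with opposite signs, and the two contrasts differ by the whole of D. A baseline difference that stays constant over time cancels from this interaction contrast. It does not cancel from the group main effect.

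**3. Type I error.** Simulated with no treatment effect, 29 ACT against 15 same-diagnosis plus 14 other-diagnosis controls, SD of change = 1, two-sided t test at 5%. D is assumed.

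| D (SD of change) | Bias (0.48D) | Type I error |
|---|---|---|
| 0 | 0 | 5% |
| 0.1 | 0.05 | about 5.4% |
| 0.2 | 0.10 | about 6.4% |
| 0.3 | 0.14 | about 8.3% |
| 0.5 | 0.24 | about 14% |

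A same-diagnosis comparison stays at 5% throughout.

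**4. Power once diagnosis is kept.** Controls are assessed only twice, so the controlled contrast is pre/post. For f = 0.25 and two moments, the standardised difference in change is d = sqrt(8f²/(1 - rho)). This is sqrt(0.5/0.7) = 0.845 at rho = 0.3 and sqrt(0.5/0.5) = 1.0 at rho = 0.5. Power is from the noncentral t with noncentrality d/sqrt(1/n1 + 1/n2).

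| Contrast | rho = 0.3 | rho = 0.5 |
|---|---|---|
| 29 vs 29 (nominal, mixed controls) | 0.89 | 0.96 |
| 29 vs 15 (within diagnosis) | 0.74 | 0.87 |
| 29 vs 14 (within diagnosis) | 0.72 | 0.85 |
| 25 vs 12 (within diagnosis, after dropout) | 0.65 | 0.79 |
| 58 vs 29 (stratified by diagnosis) | 0.96 | 0.99 |

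**The case against.** Several points on the other side are fair.

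- A reader might infer that both contrasts are certainly confounded, or are not randomised at all. The documents do not support that. About half of each control comparator is of the same diagnosis and concurrently randomised, and the time x group interaction removes stable level differences. Bias there needs untreated change to differ by diagnosis, and the article nowhere says that it does. This stands.
- Differential regression to the mean is possible but not established. Selection is on SCARED and a diagnostic interview, not on GAD-7 or SAASA. If baseline is measured after screening, some regression has already happened; the article does not settle that timing. The design section also describes both disorders as highly stable. At D of 0.1 to 0.2 the inflation is small.
- The protocol discloses the limitation and gives a reason. Disclosure stands as a point in its favour, but the planned analysis is unchanged. The reason assumes the transdiagnostic premise that Study III is meant to test, and a similar response to ACT would not imply similar untreated change on disorder-linked scales.
- A reader might also infer that the contingency control groups would be non-randomised, or that they are superfluous because randomised SAD and GAD controls already exist. The Discussion does not say how they would be recruited. With 14-15 controls per diagnosis falling short of 0.95 power, larger diagnosis-specific control groups could serve a purpose.

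The direct comparison of SAD-ACT with GAD-ACT does not use the controls, so their mixed composition does not affect it.

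**Conclusion.** The point holds in conditional form. The mismatch between allocation and analysis is on the face of the document: 2:1 within diagnosis, one mixed control group, and a three-level group factor. Each efficacy contrast loses part of the protection of randomisation and can be confounded by diagnosis. The group main effect is exposed to level differences, and the interaction to a difference in untreated 12-week change.

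The bias on change is about half that difference. Type I error runs from about 5.4% at 0.1 SD to about 14% at 0.5 SD, and all these differences are assumptions, since the document gives none. This is no omission left to a fuller plan: the article itself fixes the group factor, the pooled control group and the pairwise comparisons. It should be corrected, because it touches the main efficacy contrasts on both primary outcomes and the correction needs no new data.

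**What to change.** - Replace the three-level group factor with arm (ACT vs control) x diagnosis (SAD vs GAD) x time.
- From that one model, report the ACT effect stratified by diagnosis (58 vs 29) and the two within-diagnosis effects (29 vs about 14-15 each). The within-diagnosis effects answer the hypothesis about each intervention group.
- Restate the power of the within-diagnosis pre/post contrasts, with the correlation made explicit. For f = 0.25 before dropout it is about 72-74% at 0.3 and 85-87% at 0.5, below the stated 0.95.
- If the contingency of separate SAD and GAD control groups is kept, state its trigger and require that those controls be concurrently randomised within diagnosis, not added later.

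**Cost.** The model change uses the same participants and data. The price is precision: each diagnosis-specific contrast has about half the controls of the nominal 29 vs 29, so the sample-size statement no longer describes it. The stratified overall effect reaches about 0.96 or 0.99 power before dropout at the same two correlations.
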